### Follow‐up

10.6

Postoperative follow‐up includes investigations (CT chest and abdomen, colonoscopy) in 6 and 12 month, afterwards annually during the follow‐up period and examinations (or if in‐person contact is not possible it can be substituted by a phone call) in 30 days after surgery and afterwards every 3 month during follow‐up period. During follow‐up period complications, adjuvant treatment and recurrence are registered. Recurrence is registered when local recurrence or distant metastases are found during investigation (Colonoscopy, CT, MRI); serology recurrence is registered if CEA is 3 times higher than baseline. Quality of life will be assessed with validated questionnaires EORTC QLQ‐C30 and colorectal module CR 29 according to *Appendix*
S3 (supporting information).

Patients rejecting surgery after randomization or patients receiving different to randomization group treatment will be analysed in primary randomization groups. For patients rejecting treatment and follow‐up continuation of data collection without treatment is offered.

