Prior to comparing of group mean values in case of quantitative data, a non‐parametrical criterion of Shapiro Wilks will be used to test the normality of distribution. In case of normal distribution Student's criterion for independent samples will be used (dependant samples for quality of life assessment). For data not distributed normally non‐parametric Mann–Whitney U criterion will be implied.

Lymph node metastases pattern will be assessed as calculation of frequency of affected nodes related to number of studied nodes in each group. Correlation analysis of association of size, T‐stage, localization of the tumour with affected groups of lymph nodes, frequency of metastases, tumour budding grade, lymphovascular and perineural tumour invasion. Spearman rank correlation coefficient will be used as the data may be distributed not normally and numeric data may be included. To assess correlation of quantitative data distributed normally Pearson correlation coefficient will be implied.

For the primary endpoint and disease free survival missing data will be handled according to the survival analysis nature – censoring of the patient with the date of last contact.

Missing data for the secondary endpoints will be dealt with by using multiple imputations with Markov chain Monte Carlo method (monotone method if the data shows a monotone pattern of missing values; otherwise, fully conditional specification).

Conclusion of superiority of D3 lymph node dissection will be made in case of statistical superiority of survival during the study of D3 group over D2.

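### Disease-free survival is censored at last contact, like overall survival, so time after a patient's last investigation counts as recurrence-free although recurrence is then under-ascertained

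*Protocol article*

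**What the plan says.** Section 15 states the rule for both endpoints together: "For the primary endpoint and disease free survival missing data will be handled according to the survival analysis nature", namely "censoring of the patient with the date of last contact". DFS is then analysed by Kaplan-Meier curves and a log-rank test.

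Section 10.6 (Follow-up) describes two separate schedules:

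- **Contacts.** Examinations take place at 30 days and "afterwards every 3 month during follow"-up. If in-person "contact is not possible it can be substituted by a phone call".
- **Investigations.** CT of chest and abdomen and colonoscopy are due "in 6 and 12 month, afterwards annually during the follow"-up period.

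The event is tied to the second schedule: "Recurrence is registered when local recurrence or distant metastases are found during investigation", with colonoscopy, CT and MRI named. There is a laboratory route as well: "serology recurrence is registered if CEA is 3 times higher than baseline". For patients who reject treatment and follow-up, "continuation of data collection without treatment is offered".

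Section 12 lets patients supply results of their routine investigations. Section 14 lists outpatient files and investigation reports among the sources for the eCRF. Neither section says how DFS is censored when no such results exist.

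**The concern.** The rule is stated outright, so this is not a detail left for an analysis plan. It treats two endpoints alike although they are ascertained differently. A call settles whether a patient is alive, but not whether a CT would show a liver metastasis.

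Take a patient with a clear 12-month CT who then declines CT and colonoscopy but answers calls until year 5. The rule censors this patient at year 5. Four years enter the DFS risk set as recurrence-free, although recurrence would be recorded in them only if it came to light some other way.

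Two things are at stake. The DFS curve in each arm is too high. The comparison of arms is also distorted if patients stop investigations at different rates, which is possible because section 7.2 states that neither investigators nor patients are blinded.

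**Working it through.** The protocol gives no figure for DFS or for missed investigations, so there is no stated result to reproduce. The check is therefore an illustration of size.

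**Inputs from the protocol.** Investigations at t = 0.5, 1, 2, 3, 4 and 5 years (section 10.6); censoring at last contact (section 15).

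**Assumptions.**
- Recurrence is exponential with a true 5-year recurrence-free proportion of 70%, so S(t) = 0.7^(t/5). There are no deaths.
- A share p stops investigations by year 5 at a constant rate that is unrelated to recurrence.
- All event-free patients stay in phone contact to year 5.
- A fraction c of the recurrences missed by investigation surfaces anyway.

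**Formula.** Nobody is censored before year 5, so the Kaplan-Meier value at year 5 is one minus the proportion with a registered recurrence. The overstatement is

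B = (1 − c) × Σ ΔF_k × G_k,

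where ΔF_k = S(t_{k−1}) − S(t_k) is the probability that recurrence arises between two investigations, and G_k = 1 − (1 − p)^(t_k/5) is the probability of having stopped before the investigation that would find it.

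**Numbers.**
- ΔF = 0.03504, 0.03381, 0.06411, 0.05970, 0.05559, 0.05176 (sum 0.300).
- For p = 25%, G = 0.0284, 0.0559, 0.1087, 0.1585, 0.2056, 0.2500.
- Products: 0.00099 + 0.00189 + 0.00697 + 0.00946 + 0.01143 + 0.01294 = 0.0437, or 4.37 points when c = 0.
- The same sum gives 1.70 points for p = 10% and 2.58 points for p = 15%.

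Reported 5-year DFS under the plan's rule (truth 70%):

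| Later recurrences that surface | 10% stop | 15% stop | 25% stop |
|---|---|---|---|
| None (c = 0) | 71.7% | 72.6% | 74.4% |
| Half (c = 0.5) | 70.9% | 71.3% | 72.2% |
| 80% (c = 0.8) | 70.3% | 70.5% | 70.9% |

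Simulations with 300,000 patients per setting agree within sampling error: 71.6/72.6/74.4%, 70.7/71.3/72.2% and 70.3/70.4/70.9%. At a true 80% and c = 0, the formula gives 81.2%, 81.8% and 83.0%.

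**Between arms.** With 10% stopping in one arm, 25% in the other and no true difference, the rule alone creates 4.37 − 1.70 = 2.7 points at c = 0. This becomes 2.67 × 0.5 = 1.3 points at c = 0.5 and 2.67 × 0.2 = 0.5 points at c = 0.8.

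**Alternative rules.** These were simulated in the same model with 2,000,000 patients per setting.
- *Event-free patients censored at the last investigation, late-surfacing recurrences still counted.* The result is correct at c = 0. It falls to about 69.3/68.9/67.9% at c = 0.5 and 68.9/68.2/66.7% at c = 0.8, because events after the gap are kept while the matching event-free time is removed.
- *Both censored at the last investigation.* The result is 69.9% to 70.0% in every setting.

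**The case against.** The strongest case against the point has four parts.

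- **Recurrence can still come to light.** Section 10.6 does not say that imaging and colonoscopy are the sole route. It adds CEA, section 12 accepts outside results, and section 14 draws on outpatient files. A reader might infer that nobody is looking after the last scan, or that an event cannot then be registered. The documents do not support that. They support under-ascertainment of unknown degree, and the c = 0 row is an upper bound for each stopping rate.
- **The call replaces the examination, not the CT or colonoscopy.** This is correct. The point concerns only patients who miss those investigations. That a call counts as last contact for DFS is an inference, because contact is not defined, but nothing in the text excludes it.
- **The event definition is loose.** Section 7.3 lists recurrence and metastases, while section 15 speaks of survival without recurrence, which could include death. If death counts, a phone-only patient's death is still captured. The calculation covers the recurrence component alone.
- **Moving the censoring date can do harm.** This stands for the one-sided version, which overcorrects as shown above. It does not stand when events and event-free time share one cut-off.

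Unequal stopping between arms is a possibility in an open trial. The documents give no evidence that it will occur.

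**Conclusion.** The concern holds in a limited form. The stated rule credits time after the last investigation as recurrence-free, and other routes to registration reduce the resulting overstatement without removing it. At a true 70% with 10% to 25% stopping investigations by year 5, the overstatement is about 1.7 to 4.4 points with no later pick-up, 0.9 to 2.2 points with half, and 0.3 to 0.9 points with 80%. The true recurrence-free proportion, the stopping rates and the pick-up rates are all assumptions. The direction does not depend on them, provided that some patients stop and some later recurrences are missed.

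A reader might go further and doubt the trial's main conclusion. The documents do not support that. DFS is secondary, the primary endpoint is overall survival, last contact is the right censoring date for it, and the 768 patients were sized on survival.

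**What to change.** Split the censoring sentence in section 15:

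- **Overall survival:** keep the date of last contact.
- **DFS, event-free patients:** censor at the last investigation showing no recurrence (CT/MRI or colonoscopy, whether done under the protocol or documented from elsewhere). Phone-only contact does not extend DFS follow-up.
- **DFS, recurrences first surfacing after scheduled investigations were missed:** censor at the last investigation before the gap, so that events and event-free time are treated alike.
- **Sensitivity analysis:** report DFS censored at last contact.

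The change is a few lines of text. Investigation reports are already a source for the eCRF (section 14), so no new data are needed. The cost is that some DFS follow-up time and a few late-surfacing events drop out of the main DFS analysis. That analysis also assumes that stopping investigations is unrelated to the risk of recurrence, which is why the last-contact version should be shown beside it.

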## Control of study conduct

16

Study conduction is controlled by monitoring timing and quality of eCRF completion by representatives of main centre in National Medical Research Centre of Oncology named after N.N. Petrov, according
to part 11 of the protocol to ensure patients safety short‐term outcomes will be monitored.

In case of protocol deviation during the study main centre may suspend any centre's or surgeon's registration in the study.

The protocol of the study and all amendments, as well as informed consent are to be approved by Ethical committee of National Medical Research Centre of Oncology named after N.N. Petrov. Prior to start of the study in a certain centre, approval of local ethical committee is to be obtained.

After amendments are approved, new version of protocol with changes description is spread among principal investigators.
